### Participants

Inclusion criteria are i) permanent resident of a low-level or high-level residential care facility; ii) greater than 65 years of age; and iii) MMSE score ≤24. Exclusion criteria are i) participant's general practitioner works at more than one facility participating in the trial; ii) subject is identified by facility as medically unstable or as suffering delirium, or in the terminal stages of a co-morbid illness; iii) subject unable to participate in assessment instruments in English.

All residential care facilities (RCFs) in the Perth metropolitan area (n = 184) were sent information packages regarding the DIRECT Study. Of those, 36 agreed to participate. Participating RCFs compiled a list of residents to be screened for study participation. GPs working at the facility and residents meeting the inclusion criteria were invited to participate in the study. Study staff made second attempts to recruit GPs if residents they cared for had agreed to study participation, but the GP had not responded to the initial contact.

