### Randomisation

Randomisation will be carried out in a factorial fashion. That is care facilities and GPs will be independently randomised to intervention or control groups. Allocation will be by a centrally held computer generated randomisation table, managed by an independent statistician.

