### Sample size and statistical analysis

Training for care providers has been associated with a 0.4 point mean fall in QOL scores (SD 7.6) over 6 months, while QOL fell by a mean of 3.5 points (SD 7.9) in facilities that did not train care providers [10]. We have powered the present study to detect an effect of at least this magnitude. We would need 100 subjects in each row of the two by two factorial table (total number 200) to have 0.8 power to detect a main effect of this magnitude (alpha = 0.05; two sided). Loss of subjects to follow up, based on our previous experience, was anticipated to be in the order of 30% per annum in this population [23]. We used an estimated intra-class correlation of 0.05 (to account for clustering) and estimated cluster size of 9, resulting in an inflation factor of 1.4. We thus expected to have to enrol 364 subjects in forty clusters to achieve adequate numbers of completing subjects. This estimate of the intraclass correlation was conservative, given that intraclass correlation coefficients are typically smaller than 0.02 [24]. The power calculation was reviewed prior to closing recruitment, because actual cluster size (which influences the required number of participants) can be difficult to predict. Having recruited 67 clusters with an average cluster size of 5.2, it was confirmed that, because cluster size was smaller than anticipated, recruitment could be closed. Analysis will be by "intention to treat" (that is, according to randomisation, rather than participation in education). Statistical analysis will be conducted using multilevel mixed-effects linear regression in Stata version 11.0 (StataCorp, College Station, Texas). The effect of clustering by both facility and GP will be accounted for by treating the facility and GP as random effects with GP nested within facility. For each outcome analysis, a model containing the GP intervention, the facility intervention, and the baseline values of outcome variables will be used to estimate the marginal effect of each intervention. Next, the confounding effects of other covariates will be examined by comparing the adjusted and unadjusted intervention effects. Any covariates that produce clinically important changes in the intervention effect estimates, and are therefore demonstrably confounding these effects, will be retained in the model. Secondary analyses will be conducted to test the significance of any interaction between the facility and GP interventions. The results reported will include the estimated mean of the outcome variable in each arm of both interventions and for each intervention, the mean difference in outcome between the intervention and control arms. The results of the secondary analysis of the interaction between interventions will also be presented. All results will be presented with their associated 95% confidence intervals.

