## Results

Recruitment of 350 people with dementia, living in 39 care facilities and cared for by 55 GPs is now complete. Collection of baseline data is complete. Education has been delivered to GPs and Care staff between September 2008 and July 2009. First follow-up data collection has been completed (Figure 1). Analysis will be completed at the conclusion of second follow-up assessments after but remains blinded as second follow- up data collection is ongoing. Baseline data of participants completing the first follow-up assessment, and those lost to follow-up at the first follow-up assessment are summarised in Table 1.

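### Recruitment was closed on 67 clusters of mean size 5.2, which is neither randomised unit; at facility level clusters were as large as planned, so adequate size for the facility effect was not confirmed

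*Protocol article*

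**What the plan says.** The Randomisation section makes the design factorial: "care facilities and GPs will be independently randomised to intervention or control groups". Each of the two main effects therefore has its own unit of randomisation.

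The sample-size section takes its effect from a comparison of facilities. With training there was a "0.4 point mean fall in QOL scores (SD 7.6) over 6 months"; without it, "QOL fell by a mean of 3.5 points (SD 7.9) in facilities that did not train care providers". The unclustered requirement is put as follows: "We would need 100 subjects in each row of the two by two factorial table (total number 200"), in order "to have 0.8 power to detect a main effect of this magnitude (alpha = 0.05; two sided"). That number is inflated by 1.4 (correlation 0.05, cluster size 9) and for 30% annual loss, giving 364 residents in forty clusters.

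The same section then reports a check made before recruitment closed: "Having recruited 67 clusters with an average cluster size of 5.2, it was confirmed that, because cluster size was smaller than anticipated", recruitment could stop. It gives no power figure or revised requirement after this check.

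The Results section reports: "Recruitment of 350 people with dementia, living in 39 care facilities and cared for by 55 GPs is now complete". The Abstract has the same facility and GP counts but 351 residents, and Table 1 also adds to 351 (288 + 63). The Participants section says of the facilities approached: "Of those, 36 agreed to participate".

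**The concern.** A design effect must use the size of the clusters randomised for the comparison in question. For staff education that is the facility; for GP education it is the GP. A count of 67 is neither. Splitting the same residents into more and smaller groups lowers the design effect on paper without adding information on a comparison randomised at a higher level.

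The plan expected about forty clusters of nine, and the trial obtained 39 facilities averaging nine. At that level nothing came in smaller than planned. The apparent gain arises because a different unit was counted.

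The sentence is the article's only assurance, once recruitment was known, that the trial is large enough. A reader of a null staff-education result would rely on it.

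**Working it through.** **Inputs.** From the sample-size section: difference 3.5 − 0.4 = 3.1 points; SDs 7.6 and 7.9 (pooled 7.75); two-sided alpha 0.05; power 0.8; correlation 0.05; planned size 9; loss 30%. From the Abstract, Results and Table 1: 351 residents, 39 facilities, 55 GPs, 288 completing first follow-up.

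**Reproducing the plan.** The two-sample formula gives 99 per group, against the stated 100. The factor is 1 + (9 − 1) × 0.05 = 1.40. Then 200 × 1.40 × 1.3 = 364, and 364/9 = 40.4 clusters. The plan's target is reproduced exactly, and it shows that loss was handled by multiplying by 1.3.

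**Requirement by unit.** Factor = 1 + (m − 1) × 0.05; requirement = 200 × factor × 1.3. The last column divides by 0.7 instead of multiplying by 1.3, for comparison.

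| Unit | Mean size m | Factor | Required (× 1.3) | Required (/ 0.7) |
|---|---|---|---|---|
| 67 clusters | 5.2 (as stated) | 1.21 | 315 | 346 |
| 55 GPs | 351/55 = 6.4 | 1.27 | 330 | 363 |
| 39 facilities | 351/39 = 9.0 | 1.40 | 364 | 400 |
| 36 facilities | 351/36 = 9.75 | 1.44 | 374 | 411 |

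Enrolment was 351. By the plan's own formula the GP requirement is met and the 39-facility requirement is missed by 364 − 351 = 13.

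**Power.** Effective N = completers/factor; power = Φ(3.1 / (7.75 × √(4/effective N)) − 1.96). Example for 39 facilities under the plan's convention: 351/1.3 = 270 completers; 270/1.40 = 192.9; power 0.79.

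| Completers, and size used in the factor | 67 clusters | 55 GPs | 39 facilities |
|---|---|---|---|
| 270 (plan's × 1.3), enrolled size | 0.85 | 0.83 | 0.79 |
| 246 (30% lost), enrolled size | 0.81 | 0.80 | 0.755 |
| 246, completing size | 0.84 | 0.83 | 0.80 |
| 288 (first follow-up), enrolled size | 0.87 | 0.85 | 0.82 |
| 288, completing size | 0.88 | 0.87 | 0.84 |

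In every row the 67-cluster factor gives higher power than the facility factor, by about 4 to 6 points. With 36 facilities, power at enrolled size is 0.78 under the plan's convention and 0.74 with 30% lost.

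**Sensitivity.** At a correlation of 0.02, the level below which the article says such values typically fall, facility power at enrolled size is 0.83 (30% lost) to 0.88 (288 completers). In the other direction, a t reference on 37 degrees of freedom lowers 0.755 to 0.73 and 0.82 to 0.80. Unequal facility sizes (coefficient of variation 0.4 to 0.8, assumed) lower 0.79 to between 0.77 and 0.72.

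**The case against.** The strongest reply is that very little is missing: 13 residents, and power of 0.79 against 0.80. That is fair. Three further points also stand.

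- The lowest facility figure, 0.755, applies the enrolled cluster size to completers only. Using the completing size of 246/39 = 6.3 (factor 1.265) brings it to about 0.80.
- The planned model adjusts for baseline, whereas the calculation uses SDs of change. With equal variances the residual variance falls to (1 + r)/2 of the change-score variance. For assumed baseline-to-follow-up correlations r of 0.5 to 0.8, facility power at factor 1.40 with 30% lost becomes about 0.86 to 0.80.
- The article does not say at which level the 0.05 lies. If the 67 are GP-by-facility combinations and the correlation arises only within them, the facility factor would be nearer 1.21. That reading of the 67 is an inference. It would also mean more combinations than GPs, hence some GPs at several facilities, which fits poorly with the exclusion criterion on such GPs and with GPs nested in facilities. The flow chart (Figure 1) could not be read for this review and may define the 67.

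A reader might infer more than the document supports. One inference is that the trial is underpowered for staff education; the range above includes 80%, so that is not established. Another is that 351 is enough only when the wrong unit is used. That holds only if loss is handled by dividing by 0.7, a separate matter; under the plan's convention 351 exceeds the GP requirement of 330. A third is that a stated power figure is wrong, but none is given after the check. Nor are the effect estimates touched: the model carries random effects for both facility and GP, and results come with 95% confidence intervals.

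None of this makes the reason for closing true at facility level.

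**Conclusion.** The point holds as a correction to the stated justification for sample size. The reason given for closing recruitment is false for one of the two randomised interventions, since facility clusters averaged 9.0 as planned, and the count relied on is undefined. If the 0.05 applies between facilities, the facility comparison still requires 364 by the plan's own formula and has 351.

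Facility power at that correlation is about 0.76 to 0.84, depending on loss and on whether enrolled or completing cluster size is used; a smaller correlation or baseline adjustment would raise it. These figures assume 39 facilities of equal size and a normal reference. The upper end uses first follow-up completion, and loss by six months is not yet known. The shortfall is modest and 80% may still be reached; the calculation reported does not show that it is.

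**What to change.** Replace the sentence on closing recruitment with two statements:

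- **Facility effect:** 39 clusters, mean size 9.0, factor 1.40, requirement 364 against 351 enrolled; power about 0.76 to 0.84 at a correlation of 0.05, depending on loss and completing cluster size.
- **GP effect:** 55 clusters, mean size 6.4, factor 1.27, requirement 330, met under the plan's loss convention; power about 0.80 to 0.85 at that factor.

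Define the 67 clusters and say at which level the correlation of 0.05 applies. Reconcile 36 with 39 facilities and 350 with 351 residents; if 36 is the facility count, restate the facility line with mean size 9.75 and factor 1.44. A correlation estimated from the baseline data while analysis is still blinded may be added as a sensitivity figure only, because the correlation of baseline QOL is a rough guide to that of the baseline-adjusted outcome.

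The cost is one paragraph and, optionally, one blinded calculation on data already collected. No further enrolment and no change to the analysis are needed. The downside is that the stated position for the facility effect becomes slightly less favourable.

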**Results:**

Recruitment of 351 people with dementia, cared for by staff in 39 residential facilities and 55 GPs, was undertaken between May 2007 and July 2008. Collection of baseline data is complete. Education has been delivered to GPs and Care staff between September 2008 and July 2009. Follow- up data collection is underway.

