### Intervention

A detailed qualitative research study has been undertaken to determine the perceived needs of learners [16]. This informed development of an educational package which was delivered to GPs, clinical and direct care staff between September 2008 and July 2009. The main topics of the educational programs were:

• communication with residents and family members

• personal care and activities

• positive values

• behaviours of concern

• pain management

• dementia, depression and delirium

• effective working between GPs and RCF.

The GP education program consisted of five modules, delivered during three evening sessions. A fourth, reflective, session was also held. The sessions used case scenarios from DVDs and role plays with volunteers and professional actors to stimulate participation, consistent with adult learning principles. They were facilitated by study staff and one or two of the authors. A self-directed learning package (DVD of the first three sessions plus supporting materials), and a reflection session, were offered to GPs not attending face-to-face workshops. The GP program was approved for 40 Category 1 Continuing Professional Development points for the 2008-2010 triennium. The RCF education intervention comprised 27 brief modules which were delivered on-site at each facility by one of two educators. This format was chosen to facilitate flexibility in delivery of the program. Each of the 27 lessons was in half hour blocks which could be built into sessions of varying lengths of time. Education sessions ranged from 1 hr blocks to full 7.5 hr days.

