### Outcomes

Outcomes will be measured by blinded research assistants. Research assistants have been trained in the standard administration of assessment tools and adequate inter-rater reliability established for the QOL-AD [17].

The primary outcome of the study is the quality of life of the residents, measured using the (Alzheimer Disease Related QOL Scale (ADRQOL) [18] which relies on caregiver interview, and the QOL-Alzheimer's Disease Scale (QOL-AD) modified for use in long--term care settings [19,20] which utilizes self report and caregiver interview. Secondary outcomes include behavioural and psychologic symptoms of dementia (measured with the Neuropsychiatric Inventory- NH version [21]), use of restraint, and pain (measured using the Brief Pain Inventory modified verbal form [22]). Outcomes will be assessed at 4 weeks and 6 months after the conclusion of the educational intervention.

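### The primary model has no term for time since baseline and its covariate screen would drop one, so a possibly wide baseline-to-follow-up interval may cost precision

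*Protocol article*

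**What the plan says.** The section on sample size and statistical analysis fixes the first model: "a model containing the GP intervention, the facility intervention, and the baseline values of outcome variables will be used", with random effects for facility and for GP nested in facility. A second step follows: "Next, the confounding effects of other covariates will be examined by comparing the adjusted and unadjusted intervention effects". A covariate is kept only if it shifts an intervention estimate by a clinically important amount. No time term is named in either step.

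The calendar is given elsewhere in the article. Recruitment "was undertaken between May 2007 and July 2008" (Abstract, Results). The education package was "delivered to GPs, clinical and direct care staff between September 2008 and July 2009" (Intervention). "Outcomes will be assessed at 4 weeks and 6 months after the conclusion of the educational intervention" (Outcomes), so follow-up is timed from the end of education and not from baseline. Baseline assessments are not dated; the article says only "Collection of baseline data is complete".

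The powered effect is a difference in change over a fixed 6 months: a mean fall of 0.4 points where care providers were trained, "while QOL fell by a mean of 3.5 points (SD 7.9) in facilities that did not train care providers".

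**The concern.** The sample size rests on change over 6 months, but the schedule does not hold the baseline-to-follow-up interval at 6 months or at any other constant. A resident recruited early and followed late has had far longer to decline than one recruited late and followed early, yet the model treats their baseline scores as equally current.

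The screen does not repair this. It looks for confounding, meaning movement in the intervention estimate. A covariate that strongly predicts the outcome but is balanced between arms leaves the estimate where it was and is dropped, and its gain in precision goes with it. Elapsed time in a declining population is that kind of covariate. The objection is therefore to a rule the article states, and not to detail it leaves out.

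Facilities compiled their own screening lists and received education on site, so residents of one facility may share much of their interval. Unequal decline would then appear as between-facility variance, the component that limits precision for the facility effect.

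**Working it through.** **Inputs from the article.** Falls of 0.4 (SD 7.6) and 3.5 (SD 7.9) points over 6 months; two-sided alpha 0.05; ICC 0.05; cluster size 9; loss 30% a year; 39 facilities; 351 residents, of whom 288 completed first follow-up and 63 were lost; the recruitment and education windows above.

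**1. The plan's own figure.** Pooled variance = (7.6² + 7.9²)/2 = 60.085, SD 7.75. Target difference = 3.5 − 0.4 = 3.1. n per arm = 2 × 60.085 × (1.960 + 0.842)² / 3.1² = 98.1, that is 99, against the stated 100. Inflation = 1 + 8 × 0.05 = 1.4, and 200 × 1.4 × 1.3 = 364, as stated. The inputs are read correctly.

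**2. Interval to first follow-up, assuming baseline at recruitment.** Shortest: July 2008 to September 2008 plus 4 weeks, about 3 months. Longest: May 2007 to July 2009 plus 4 weeks, about 27 months. These are outer bounds, because each pairs the extremes of two windows.

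**3. Drift over that 24-month spread.** Slow: 0.4/6 = 0.067 points a month, giving 1.6 points. Fast: 3.5/6 = 0.583 a month, giving 14.0 points. The target effect is 3.1.

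**4. SD of the interval.** Assume dates uniform over the windows, taken as 14 and 10 months. Recruitment spread alone: 14/√12 = 4.04 months. Education spread alone: 10/√12 = 2.89. Both: √(4.04² + 2.89²) = 4.97.

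**5. Power for the facility effect.** Assume linear decline and intervals that vary wholly between facilities. Let D = rate × SD of interval. Then:
- total variance V = 60.085 + D²
- ICC = (0.05 × 60.085 + D²)/V
- design effect = 1 + (288/39 − 1) × ICC
- SE = √(4 × V × design effect / 288)
- power = Φ(3.1/SE − 1.96)

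With D = 0: design effect 1.32, SE 1.05, power 0.84. Worked example, fast rate with both windows: D = 2.90, V = 68.5, ICC = 0.166, design effect 2.06, SE 1.40, power 0.60.

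| Decline per 6 months | Interval SD (months) | D (points) | ICC | Power |
|---|---|---|---|---|
| 0.4 | 4.04 to 4.97 | 0.27 to 0.33 | 0.05 | 0.84 |
| 1.75 (half the fast rate) | 4.04 to 4.97 | 1.18 to 1.45 | 0.07 to 0.08 | 0.79 to 0.77 |
| 3.5 | 2 to 3 | 1.17 to 1.75 | 0.07 to 0.10 | 0.79 to 0.74 |
| 3.5 | 4.04 to 4.97 | 2.36 to 2.90 | 0.13 to 0.17 | 0.67 to 0.60 |

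Counting the windows as 15 and 11 calendar months and keeping cluster size 9 gives a fall from 0.82 to 0.52 at the fast rate, and to 0.81 at the slow rate.

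**6. Chance imbalance.** With 39 facilities split about equally, the arm difference due to drift has SD 2D/√39: about 0.1 points at the slow rate and 0.76 to 0.93 at the fast rate.

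**7. Check against observed loss.** 63/351 = 18%. At 30% a year this corresponds to 12 × ln(0.82)/ln(0.70), about 6.7 months. Uniform dates over both windows imply a mean interval of about 15 months and a loss of 1 − 0.70^(15/12) = 36%. Either typical intervals were well short of the upper bound, or attrition was lower than assumed.

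**The case against.** **Interval length.** A reader might infer that baseline scores were in fact up to 27 months old. The article does not support that. It dates recruitment and not assessment, nothing shows that the earliest recruits were the last to be followed, and the 18% loss sits more easily with shorter intervals. The range is what the dates permit.

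**Bias.** A reader might also infer that the treatment comparison is biased. That is not shown. Facilities and GPs were randomised, so recruitment timing is balanced in expectation, and the facility random effect carries between-facility drift into the standard error. An interval that differed enough between arms to move the estimate is also what the second step is designed to retain. Systematic bias would need follow-up in control facilities to be timed differently, and the article is silent on that timing.

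**Power.** The larger losses stack assumptions: the faster of two decline rates, linear over many months; intervals varying wholly between facilities; and a starting ICC of 0.05 that the article itself calls conservative. Starting from 0.02 at half the fast rate, power is 0.85 to 0.82. This limits the certain size of the problem but does not remove it, because the fast rate is the one the sample size assumes for untrained facilities.

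**Scope.** Covariate lists and visit windows commonly sit in the full protocol or SAP. That is fair, but the retention rule is stated here, and as stated it drops a balanced prognostic covariate.

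**Adjusting for the full interval.** Its end point depends on when education concluded, which is after randomisation and could differ by arm. This objection stands and shapes the remedy.

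**Conclusion.** The point holds as one of precision. The published dates allow the baseline-to-follow-up interval to vary widely, the primary model has no term for it, and the stated screen would discard elapsed time unless it happened to move the intervention estimate. The cost for the facility effect runs from negligible (power about 0.84 at 0.4 points per 6 months) to substantial (about 0.60 to 0.67 at 3.5 points per 6 months), with chance imbalance between arms to match. The upper end assumes baseline at recruitment, dates uniform over the windows, linear decline, and intervals varying mainly between facilities. None of these can be confirmed from the article. Neither systematic bias nor an invalid test is established. The change is worth making because it is cheap and the analysis is still described as blinded; confidence in the size is moderate at best.

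**What to change.** In the statistical analysis section, before unblinding:

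1. Add one linear time term to the primary model for every outcome, prespecified and exempt from the confounder screen. Base it on the baseline assessment date, for example months from each resident's baseline to one calendar date common to all, such as the start of the education programme in September 2008. Education cannot affect that quantity.
2. As a sensitivity analysis, replace it with the full interval from baseline to the follow-up assessment.
3. Report the distribution of the full interval by arm for both interventions, and state how follow-up was timed in control facilities and for control GPs.

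The cost is one extra model term and no new patient contact, provided assessment dates were recorded, which the article does not say. If intervals prove similar, little is gained and little is lost. The term in item 1 addresses only the recruitment spread. In the fast, two-window case the remaining 2.89-month education spread gives D = 1.68 points and ICC 0.09, so power would recover from about 0.60 to about 0.75, short of the full 0.84.

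### Covariates are retained according to how far they move the intervention effect, and no primary model is named; name one model before unblinding

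*Protocol article*

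**What the plan says.** The Sample size and statistical analysis section of the protocol article builds the model in two steps. The first step is fixed in advance for every outcome: "a model containing the GP intervention, the facility intervention, and the baseline values of outcome variables will be used to estimate the marginal effect". The second step brings in further covariates, and the article describes it in these terms: "the confounding effects of other covariates will be examined by comparing the adjusted and unadjusted intervention effects". Whether such a covariate stays is then decided by the size of the shift it causes: "Any covariates that produce clinically important changes in the intervention effect estimates, and are therefore demonstrably confounding these effects, will be retained".

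The section then turns to output: "The results reported will include the estimated mean of the outcome variable in each arm of both interventions", together with mean differences and 95% intervals. Nothing links that output to the first-step model or to the model left after the second step.

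The Randomisation section states that "care facilities and GPs will be independently randomised to intervention or control groups".

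**The concern.** Keeping a covariate because it changes the estimate is a method for finding confounders in observational data. Here the exposure is randomised, so calling such a covariate a demonstrated confounder is the wrong description. Among all randomised residents the imbalance is due to chance; among completers, differential loss could add to it.

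Two things follow. The composition of the final model depends on the quantity the trial is meant to estimate, seen by arm. The rule also has no criterion for prognostic strength, which is what determines the gain from adjustment. Because it is applied outcome by outcome, covariate sets may differ between analyses. Table 1 lists five quality-of-life ratings and the Outcomes section gives two follow-up times, so up to 5 × 2 = 10 quality-of-life models could carry different covariates.

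At stake are a clearly identified primary estimate, intervals that mean what they say, and some precision.

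**Working it through.** **1. What the rule selects on.** For a least-squares model with one added covariate X,

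unadjusted effect − adjusted effect = b × (mean of X in intervention − mean of X in control),

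where b is the slope of the outcome on X given arm. With the baseline outcome already in the model, the bracket is the imbalance left after allowing for it. Randomisation gives the bracket expectation zero, so retention depends on b times a chance difference. The precision gain depends on b alone.

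Example: take an SD of 7.75 (step 2), a correlation of 0.3 and a retention threshold of 0.5 points (the last two assumed). The slope is 0.3 × 7.75 = 2.3 points per SD of X. The covariate is kept only if the arms differ by at least 0.5 / 2.3 = 0.22 SD. An equally prognostic covariate with better balance is dropped.

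**2. The plan's own figure.** The rule has no stated number, but the simulations rest on the design effect size, so that was reproduced first. The section reports that "Training for care providers has been associated with a 0.4 point mean fall in QOL scores (SD 7.6) over 6 months" and that scores fell by 3.5 (SD 7.9) without training.

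- Difference: 3.5 − 0.4 = 3.1.
- Pooled SD: √((7.6² + 7.9²)/2) = 7.75.
- For 80% power at two-sided 5%, n = 2 × (1.96 + 0.84)² × 7.75² / 3.1² gives 99 per row after rounding up. With 100 per row, power is 0.807.

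The stated 100 per row is confirmed.

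**3. Simulations of the rule.** Both used regressions on cluster means with ICC 0.05.

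- Simulation A: 39 facilities with about 7 completers each (288 / 39 = 7.4); 4,000 to 8,000 replicates.
- Simulation B: 288 completers in 38 or 66 clusters; thresholds of 0.31, 0.5 or 1.0 points; 4,000 null and 2,000 alternative runs per setting.

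The covariates are assumed. In B they are 5 or 8 independent covariates, each correlated 0.2 or 0.3 with the outcome. They explain 5 × 0.2² = 20%, 5 × 0.3² = 45% or 8 × 0.3² = 72% of the variance.

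Type I error at nominal 5%:

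| Analysis | A | B |
|---|---|---|
| Fixed list | 4.6 to 4.8% | 4.4 to 5.6% |
| Rule applied mechanically | 4.1 to 5.6% | 2.1 to 5.8% |
| Selective use | 8.8 to 10.2% | 5.1 to 14.5% |

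The Monte Carlo standard error at 5% with 4,000 runs is √(0.05 × 0.95 / 4000) = 0.3 points. Selective use means settling on the most favourable candidate model (A), or keeping only covariates that move the effect away from zero (B). The extremes of 2.1% and 14.5% both come from the 72% setting with the smallest threshold.

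Power at 3.1 points with five covariates:

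| Variance explained (assumed) | Fixed list | Rule |
|---|---|---|
| 20% (B, 38 clusters) | 0.84 | 0.81 to 0.82 |
| 30% (A) | 0.85 | 0.80 to 0.83 |
| 45% (B, 38 clusters) | 0.95 | 0.82 to 0.90 |

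In A the mean standard error was 0.97 with the fixed list and 1.04 to 1.06 under the rule. Intervals are thus about 7 to 8% narrower with the list (0.97 / 1.04 = 0.93; 0.97 / 1.06 = 0.92). In B the rule kept on average 0.01 to 2.4 of the 5 to 8 covariates, although all were prognostic by construction.

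**The case against.** Three stronger readings are tempting, and the article supports none of them.

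- A reader might infer that the headline result will come from the selected model. The retention wording leans that way, but the first-step model is fully fixed and is itself said to estimate the effects. The text leaves the choice open.
- A reader might infer a false-positive rate near 10%. That figure models an analyst who picks favourably. The article describes no such thing: its rule covers changes in either direction, and applied that way it is not anti-conservative to any material extent.
- A reader might infer that prognostic information is thrown away wholesale. The baseline outcome, probably the strongest predictor, is always in the model. Only the other covariates are exposed.

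It is also fair to say that a condensed article may leave a numerical threshold and a covariate list to the full protocol or analysis plan. Their absence is not held against it. Supplying them would not cure the point, however, because selection on the effect would remain.

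Speaking of confounding is not wholly unreasonable among completers. Table 1 shows 63 of 351 residents (18%) lost at first follow-up, with 44% men among those lost against 20% among completers. The table is not split by arm, so differential loss is neither shown nor excluded. That supports adjusting for covariates named in advance; it does not support choosing them by the shift they cause.

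Finally, the simulations are simpler than the planned mixed model with GP nested in facility, and they give no separate result for the GP intervention. The design SDs describe change over 6 months, so the assumed variance explained would have to come on top of the baseline outcome. These objections limit the size of the point, not its substance.

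**Conclusion.** The point holds as a badly chosen rule combined with an unnamed primary model. It should be fixed, but it does not threaten the trial's validity.

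Applied mechanically, the rule leaves type I error at about 2 to 6%. Its cost is precision: 0.80 to 0.83 power against 0.85 if five covariates explain 30% of the variance, and nearer 0.02 to 0.03 if they explain 20%. The article gives no figure for variance explained, so these sizes are illustrative. Under the 30% assumption, power with the rule still meets the design aim "to have 0.8 power to detect a main effect of this magnitude (alpha = 0.05; two sided"). Inflation of type I error depends on selective use of the retention judgement, which the article does not describe but which a named model would rule out.

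**What to change.** Before unblinding, delete the retention rule and name one primary model for each outcome. Either choice is sound:

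- the model already specified, with both interventions and the baseline outcome; or
- that model plus a short fixed list of prognostic covariates recorded at baseline, for example age, sex and MMSE, all shown in Table 1.

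Report the other as a sensitivity analysis, and state that the means, differences and 95% intervals come from the primary model. Level of care appears in the eligibility criteria but not in Table 1, so confirm that it was recorded before listing it.

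The change is still open, since the Results section says the analysis remains blinded. It costs one sentence, plus a few degrees of freedom if covariates are added.
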